### Objectives

Thus, the current study aimed to close this research gap. This paper describes the protocol for a multicenter randomized-controlled trial with the following research questions:Is the stepped-care home treatment approach “HoT” superior to treatment as usual (TAU) when applied as continuous IP or stepped-care IP/DP in improving body mass index (BMI) at 12 months after hospital admission (primary outcome), AN, and general psychopathology; avoiding rehospitalization, and increasing treatment motivation, quality of life, satisfaction with treatment of both patients and caregivers (secondary outcomes)? Is patient safety ensured during HoT?Is HoT less expensive than TAU in terms of direct costs during differential treatment, i.e., between randomization and discharge?How feasible is HoT, and how do the staff of child and adolescent psychiatric hospitals accept the treatment method of HoT (visiting the patient and his or her family at home) as a precondition for implementing HoT in common departments for child and adolescent psychiatry? How do caregivers’ burden and skills change during HoT?Can this new stepped-care home treatment approach “HoT” be applied to the broad range of young patients with AN who are admitted to hospitals in Germany? How similar are German AN patients in general to the patients in the RCT, and how many could be expected to be suitable for HoT? Can this treatment modality potentially be of widespread importance/be applied to a relevant proportion of treatment-requiring AN patients?

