### Treatment as usual

The patients randomized into the TAU arm either stay in IP or are transferred to DP depending on individual needs or the usual treatment and situation at the respective center. TAU is continued for as long as it is individually necessary to achieve the target weight and sufficiently improve regarding cognitive, affective and behavioral symptoms of the ED (Table 2).

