### Criteria for discontinuing or modifying allocated interventions

When parents/patients discontinue treatment prematurely (e.g., discharge against medical advice), they are asked to still participate in the 9- and 12-month follow-up assessments to enable intention-to-treat analysis. Discontinuation of HoT may occur if one of the following criteria apply: (1) lack of compliance (if the patient or parents/legal guardians do not comply with the recommendations of the team (e.g., multiple appointment cancellations), (2) risks to patient safety (including serious medical complications, refusal to eat, suicidality, other serious adverse events that indicate a potential health hazard for the patient, insufficient weight gain, or other safety reasons which, in the opinion of the clinical team, preclude further treatment at home), or (3) the patient’s or parents’ wish to terminate home treatment (e.g., due to perceived burden on the family, increased conflicts, or other reasons). After discontinuing HoT, the patient is offered rehospitalization and treatment according to standard care. However, a short-term crisis leading to readmission of ≤ 7 days during HoT does not necessarily lead to a complete termination.

If patients or their legal guardians withdraw their consent for participation, HoT is discontinued and no further outcome assessments are performed, but standard treatment (e.g., as inpatients) is offered. For patients in the TAU arm, it is not possible to switch to HoT (as this is not a routinely offered treatment modality in Germany).

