#### Families/patients

The treatment sessions are arranged with the family a week ahead of time. Patients or carers may receive additional appointments depending on their individual needs. In addition, to improve adherence, families and patients have the possibility of calling members of the treatment team during the day and the child and adolescent psychiatrist on call outside working hours. In the case of a crisis, a short-term hospitalization is possible at all sites to ensure patient and family adherence and safety.

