### Statistical methods

#### RCT

The superiority of the HoT arm over the TAU arm will be analyzed for the primary endpoint (BMI 1 year after admission) using a linear mixed model for repeated measures in which study arm, sex, BMI at admission and at randomization, and age are included as fixed effects, and center and subject ID are included as random effects. All assessments of BMI after randomization (at discharge and at the 9- and 12-month follow-up timepoints) are considered repeated outcomes (the dependent variable); thus, time point is also included as a fixed effect. The difference between the achieved BMI in both study arms at the 12-month follow-up is the parameter of interest. Re-admissions are considered intercurrent events [62] and are handled depending on the timing of readmission. For patients who were readmitted to IP due to an eating disorder during follow-up and who were still in in- or day-patient treatment at the time of the 12-month follow-up assessment or discharged within the 4 weeks prior, we will use the BMI at readmission instead of that at follow-up to obtain a conservative estimate of their BMI. A subgroup analysis for patients with AAN (admission BMI ≥ 10th percentile) will be performed for the primary outcome. In addition, (serious) adverse events ((S)AEs) are tabulated by study arm and in relation to treatment as assessed by the investigator. No statistical tests will be performed for (S)AEs. Secondary endpoints are investigated with analogous logistic, linear or time-to-event (for time to readmission) models, depending on the type of endpoint.

The statistical evaluation of the RCT is carried out according to the intention-to-treat principle: all randomized study participants are included in the statistical analysis, regardless of whether the treatment was completed. In addition, an analysis only of patients treated in accordance with the protocol—i.e., without relevant protocol violations (per protocol set)—will be performed as a sensitivity analysis for the primary outcome. In general, the mixed model for repeated measures analysis can also be applied if some of the outcome data are missing. Further sensitivity analyses considering missing values will be performed.

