### Adverse event reporting and harms

In the pilot study with 22 patients, HoT was a safe treatment method. Except for deliberate self-harm which often occurs in adolescent patients presenting with an ED [63] no serious adverse events occurred [31]. In the present study, adverse events (AEs) or serious adverse events (SAEs) are documented, assessed, and reported according to GCP guidelines. SAEs are reported to the sponsor representative within 24 h. In the current multicenter trial, several precautions are taken to ensure the participant safety. First, the treatment centers were chosen based on their extensive and long-standing experience in treating adolescent patients with AN in IP and OP treatment settings. Second, each HoT staff member must have previous experience in treating adolescent patients with AN and must attend specific trainings. Additionally, close specialist supervision of the coordinating center and regular organizational meetings with clinical managers and senior psychiatrists is performed to address these challenges. In the case of a serious adverse event, an advisory board of two external experienced ED experts ([name]. [name] of Tübingen, Germany, and [name]. [name] of Hannover, Germany) review each case to recommend whether the trial should be continued and/or further measures of safety need to be implemented. The final decision in such cases lies with the PI as the sponsor representative. Insurance coverage for general harm exists through the liability insurance of the respective participating center. In addition, an insurance covering travel to and from the assessments at the respective centers has been established.

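### During the treatment phase, the by-arm SAE count may partly reflect place of care: an event serious only through admission can arise in a HoT patient at home but hardly in a TAU patient still on the ward

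*Protocol article*

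**What the plan says.** All of this is in the protocol article.

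- **Analysis.** Under Statistical methods, RCT, "serious) adverse events ((S)AEs) are tabulated by study arm and in relation to treatment as assessed by the investigator". The same paragraph adds "No statistical tests will be performed for (S)AEs". The table is therefore descriptive, and the counts are what a reader will compare.
- **Definition.** Under Adverse event reporting and harms, "adverse events (AEs) or serious adverse events (SAEs) are documented, assessed, and reported according to GCP guidelines". The article does not list the grounds of seriousness. Two external experts review each SAE case and advise on whether the trial should continue.
- **Question served.** The Objectives ask: "Is patient safety ensured during HoT"?
- **HoT arm.** Patients leave the ward for 12 to 16 weeks of home treatment. Under Criteria for discontinuing or modifying allocated interventions, "a short-term crisis leading to readmission of ≤ 7 days during HoT does not necessarily lead to a complete termination", and patients whose HoT is stopped are offered rehospitalization. Under Families/patients, "In the case of a crisis, a short-term hospitalization is possible at all sites to ensure patient and family adherence and safety".
- **TAU arm.** Patients remain inpatients or move to day care. Under Treatment as usual, "TAU is continued for as long as it is individually necessary to achieve the target weight", and Table 2 gives TAU no specified length.

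**The concern.** The two arms differ by design in where the patient sleeps. One commonly used ground of seriousness, new or prolonged hospitalization, depends on exactly that. A HoT patient who goes into crisis or gains too little weight and is taken back onto the ward has a new admission. A TAU inpatient with the same course is already in hospital. Because the TAU stay has no planned end, a prolongation is hard to recognise. The same clinical event can therefore be an SAE in one arm and a non-serious AE, or no recorded event, in the other.

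At stake is how the by-arm table is read. It bears on a stated research question about safety and carries no test or interval. The only further split the article states is the investigator's judgement of relatedness. That judgement does not address the ground of seriousness, and it is made in a trial where study staff cannot be blinded.

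**Working it through.** The article states no SAE rate, no crisis rate and no readmission rate during HoT, so there is no figure of the plan to reproduce. The check has three parts.

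**1. The same event in each setting**

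| Event | HoT, at home | TAU, on the ward | TAU, day patient |
|---|---|---|---|
| Serious by its nature | can count | can count | can count |
| Serious only through new admission | can count | cannot arise | can count |
| Serious only through prolonged stay | only during a readmission | possible, but no planned end to measure against | not while in day care |
| Non-serious AE | can count | can count | can count |

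The asymmetry lies mainly in the second row and applies only to TAU patients who are still inpatients. Insufficient weight gain shows it most clearly. The article lists it as a safety reason for stopping HoT, after which rehospitalization is offered, while a TAU inpatient with the same problem simply stays.

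**2. Illustrative size during 12 to 16 weeks of HoT**

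Inputs: 82 patients per arm (Abstract), 12 to 16 weeks (HoT), and two readmission rates from Background and rationale. One is about one third within 1 year of inpatient discharge. The other is about 30% over 2½ years in the investigators' day patient trial. Neither is a rate during HoT, so applying them is an assumption. With a constant hazard, h = −ln(1 − p)/T, and the proportion readmitted by week t is 1 − exp(−h·t).

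- One third in 52 weeks: h = ln(1.5)/52 = 0.00780 per week. At 12 weeks this gives 8.9%, and 82 × 0.089 = 7.3 patients. At 16 weeks it gives 11.7%, or 9.6 patients.
- 30% in 130 weeks: h = −ln(0.7)/130 = 0.00274 per week. At 12 weeks this gives 3.2%, or 2.7 patients. At 16 weeks it gives 4.3%, or 3.5 patients.

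The range is about 3 to 10 of 82 HoT patients. The matching number for TAU patients still on the ward, by new admission, is 0.

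The gap also depends on how many TAU crises count by some route (prolonged stay, transfer from day care to the ward, or the nature of the event). Assume a 10% crisis rate in both arms and that every HoT crisis is admitted and counted. HoT then shows 82 × 0.10 = 8.2. If 0%, 25%, 50% or 100% of TAU crises count, TAU shows 0, 2.1, 4.1 or 8.2. The gap runs from the whole HoT count to nothing.

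**3. What follow-up does to the contrast**

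Inpatient stabilization of 5 to 8 weeks plus HoT of 12 to 16 weeks ends at weeks 17 to 24 and leaves 35 to 28 weeks to month 12. Suppose TAU discharge falls at a similar time (assumption). The higher hazard then adds 82 × (1 − exp(−0.00780 × 28)) = 16.1 to 82 × (1 − exp(−0.00780 × 35)) = 19.6 admissions in each arm. Pooled over both phases, the 12-week case reads 7.3 + 19.6 = 26.9 against 19.6, a ratio of 1.4. The 16-week case reads 9.6 + 16.1 = 25.7 against 16.1, a ratio of 1.6. An unsplit table would therefore dilute the tilt and also hide the phase it comes from.

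**The case against.** The strongest objection is that the decisive step is not in the article. It refers to GCP and lists no criteria. No sentence says that a crisis readmission in HoT is an SAE, or that the same crisis on the ward is not. This is a condensed report of protocol version 5, and the full protocol may exempt admissions for the underlying illness. That stands as a condition: if admission alone does not confer seriousness in this trial, the point falls.

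The article also points to seriousness by content. It lists serious medical complications, refusal to eat and suicidality alongside other serious adverse events, and it names self-harm as the exception to an otherwise SAE-free pilot. Such events can be counted on a ward. This stands, but it does not cover an event that becomes serious only through admission.

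The pilot also argues for a small effect. With 22 patients, the higher rate predicts 22 × 0.089 = 2.0 to 22 × 0.117 = 2.6 admissions. The chance of none is about 13% to 6%, and no SAE other than self-harm was reported. The lower rate predicts 0.7 to 0.9, with a chance of none of about 48% to 38%. The pilot therefore fits a low rate, or a practice of not classing such admissions as SAEs, at least as well.

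Rehospitalization is a separate secondary outcome and non-serious AEs are tabulated too, so some of this can be seen elsewhere. Neither removes admission-driven events from the SAE count.

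A reader might go further and infer that the table compares place of care rather than harm, or that the experts receive a signal almost only from HoT. The documents support neither. TAU day patients and both arms after discharge can be newly admitted, and the article provides for recording adverse events at the follow-up visits. Events serious by nature count in both arms. The experts review each case, with its reasons, rather than a count.

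**Conclusion.** The point holds in a limited form. Between randomization and discharge, the by-arm SAE count may be partly driven by place of care, so a HoT excess in that count would not by itself show more clinical harm. The size cannot be determined from the article. The illustration is about 3 to 10 of 82 HoT patients whose event could not arise by new admission in a TAU patient still on the ward.

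This rests on three assumptions: that hospitalization alone can make an event serious under the standard the article adopts, that the background readmission rates carry over to the HoT period, and that the hazard is constant. A larger share of TAU patients in day care, pooling with follow-up, or an exemption in the full protocol would each shrink the gap.

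It does not follow that admissions from home should be left out of the safety comparison. An emergency admission during HoT bears directly on whether patients are safe at home. The fault is that the stated table mixes it with events that both arms can generate equally. This is a cheap improvement to a descriptive analysis and does not undermine the trial.

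**What to change.** In Statistical methods, RCT, keep all SAEs in the by-arm table and add the following:

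- Split SAEs by ground of seriousness: hospitalization or prolongation only, versus any other ground. State that the hospitalization-only row is not directly comparable between arms.
- Split by phase: randomization to discharge, versus follow-up.
- Classify crisis readmissions, prolonged stays and transfers from day care to the ward by one written rule that applies to both arms. If the full protocol already has such a rule or an exemption, cite it.
- Beside the SAE table, show clinical events already recorded as AEs (for example suicidality, self-harm, refusal to eat, serious medical complications), counted identically wherever the patient is.

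SAE reporting, the experts' case review and clinical management stay unchanged. The cost is analysis-plan wording, one more table, and coding of existing SAE and AE forms, including TAU ward events. No new visits or staff are needed.

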#### Cost analysis

For the statistical evaluation of the cost data, cost from randomization to discharge will be compared between the study’s arms using a linear model with baseline covariates analogous to those for other quantitative outcome measures. Total costs from admission to discharge will also be reported for health insurance reasons.

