Outpatient treatment (OP) is considered the first-line treatment in children and adolescents with AN [8, 9]. While OP is recommended as the first choice of treatment for adolescents with AN, approximately half of these patients require more intensive care, generally inpatient treatment (IP) [10]. Although IP is often effective in achieving weight gain [11, 12], it is not always sufficiently effective in modifying disordered eating behavior and other symptoms of AN [13]. In addition, long hospitalizations impede the age-appropriate social development of adolescents with AN [14]. On the other hand, shorter IP approaches with primarily nutritional and somatic stabilization are often still associated with high levels of stress and symptoms of depression and anxiety upon discharge from the hospital [15], limiting the potential impact of simply shortening IP. Generally, after discharge from IP, almost all patients with AN initially struggle to maintain a healthy weight, and many patients relapse into disordered eating behaviors such as food restriction and excessive exercising, followed by another round of weight loss [16]. Approximately one third of adolescents with AN who undergo at least one inpatient treatment require rehospitalization within 1 year after discharge [17, 18]. In our own randomized-controlled trial (RCT) on day patient treatment, approximately 30% of patients required a second admission to the hospital during a 2½-year follow-up [19]. In addition, inpatient treatment is associated with the highest treatment costs compared to other treatment modalities [20]. Given the very high readmission rates after IP [21, 22] and increased hospital admissions of children and adolescents with AN—especially during the COVID-19 pandemic [23, 24]—innovative ideas are desperately needed.

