### Cost analysis

Direct costs for the health insurance institutions of the differential treatment period, i.e., between randomization (start of HoT/TAU) and discharge, will be collected and will be compared between the treatment arms.

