#### Cost analysis

Regarding the cost analysis, the direct costs of treatment (TAU vs. HoT between randomization and discharge) are collected from the centers.

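### The cost comparison ends at discharge, so readmission costs up to 12 months are left out in both arms; this limits what a finding that HoT is less expensive can mean

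*Protocol article*

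**What the plan says.** The article fixes the same cost window in four places.

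- **Objectives:** "Is HoT less expensive than TAU in terms of direct costs during differential treatment, i.e., between randomization and discharge".
- **Cost analysis, among the intervention sections:** "Direct costs for the health insurance institutions of the differential treatment period, i.e., between randomization (start of HoT/TAU) and discharge, will be collected".
- **Outcomes, Cost analysis:** the data source is the sites ("TAU vs. HoT between randomization and discharge) are collected from the centers").
- **Statistical methods, Cost analysis:** "cost from randomization to discharge will be compared between" the arms, in a linear model with baseline covariates. The only other figure has the same end point: "Total costs from admission to discharge will also be reported for health insurance reasons".

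Three other statements bear on this window.

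- **Criteria for discontinuing or modifying allocated interventions:** "After discontinuing HoT, the patient is offered rehospitalization and treatment according to standard care". A crisis readmission of at most 7 days "does not necessarily lead to a complete termination" of HoT.
- **Background and rationale:** "Approximately one third of adolescents with AN who undergo at least one inpatient treatment require rehospitalization within 1 year after discharge". The same paragraph names inpatient care as the setting with the highest costs.
- **Abstract:** number and duration of psychiatric rehospitalizations are a secondary outcome. Follow-up runs to T5, 12 months after admission. Neither is linked to the cost comparison.

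**The concern.** Discharge is a post-randomization date that depends on how treatment goes. Both arms continue until target weight is reached and held and symptoms have eased. HoT is planned for 12 to 16 weeks, while TAU has no set length. The arms are therefore costed over periods of different length, set partly by outcome.

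Two kinds of cost are affected.

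1. **Readmission after discharge, in either arm.** This is left out under any reading of the text. It is also an event that HoT is hoped to reduce.
2. **Ward care after HoT is stopped.** Reasons for stopping include insufficient weight gain and refusal to eat. The article does not say whether discharge is then the end of HoT or the end of the ward stay that follows. Under the first meaning, a patient who fails early has a short, cheap costed period, and the expensive care that follows is not counted.

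What is at stake is how the result will be used. The findings go to the innovation fund, and statutory insurers would pay for HoT in routine care. Such readers may take lower cost to mean lower cost over the year, which this window cannot show.

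**Working it through.** The article gives no cost figure, unit cost or power for the cost comparison, so there is no planned number to reproduce. The check covers the timeline and the volume of care outside the window.

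**Uncosted time after regular HoT.** Inputs from the article: stabilization 5-8 weeks, HoT 12-16 weeks, T5 at 12 months (52 weeks) after admission.
- Earliest regular discharge: 5 + 12 = week 17. Latest: 8 + 16 = week 24.
- Weeks left to T5: 52 − 24 = 28, up to 52 − 17 = 35.

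**Readmission care left out by T5.** The one-third rate runs for a year after discharge, but T5 falls 12 months after admission, so the rate must be scaled to the remaining weeks. Assumptions: readmissions spread evenly over the year; stays of 8-13 weeks (not in the article).
- Share readmitted by T5: 1/3 × 28/52 = 18%, up to 1/3 × 35/52 = 22%.
- Inpatient weeks per patient: 0.18 × 8 = 1.4, up to 0.22 × 13 = 2.9.

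Early clustering of readmissions would raise the share; stays running past T5 would be cut off and lower the weeks.

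**Lower rate as a sensitivity check.** The article also reports about 30% readmitted over 2½ years (130 weeks) in the group's own day-patient trial. Spread evenly:
- Share by T5: 0.30 × 28/130 = 6.5%, up to 0.30 × 35/130 = 8.1%.
- Inpatient weeks per patient: 0.065 × 8 = 0.5, up to 0.081 × 13 = 1.05.

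**Failed HoT, if discharge means the end of HoT.** Illustration only. Unit: the cost of one inpatient week. Assumptions: a HoT week costs *r* = 0.5; a share *f* = 20% fail, at HoT week 4; the following ward stay lasts *L* = 8-12 weeks; regular HoT lasts 14 weeks (midpoint of 12-16).
- Nobody fails: 14 × 0.5 = 7.0.
- Counted with failures: (1 − 0.2) × 7.0 + 0.2 × 4 × 0.5 = 5.6 + 0.4 = 6.0.
- Not counted: 0.2 × 8 = 1.6, up to 0.2 × 12 = 2.4.
- Full cost: 6.0 + 1.6 = 7.6, up to 6.0 + 2.4 = 8.4.

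Over *r* = 0.3-0.7 and *f* = 10-30%, failure lowers the counted mean by 0.3-2.1 units while 0.8-3.6 units go uncounted. In every scenario, failure lowers the counted cost and raises the full cost. If discharge instead means the end of the whole index episode, including the return to the ward, this part disappears and only readmission after discharge is missing.

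**The case against.** The strongest reply is that the scope is declared and consistent. The objective asks about cost during differential treatment only, and every later section uses that window. This stands: the analysis answers the question posed, and a reader who infers a contradiction between objective and analysis would be wrong.

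A reader might also infer that the window is tilted toward HoT. The document does not support that. If HoT prevents relapse, leaving out readmissions hides part of its saving, and early exit from TAU shortens the TAU period as well. The net direction is unknown.

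Nor does the text establish that ward costs after failed HoT are lost. That depends on a definition of discharge which the article does not give and which the full protocol or analysis plan may settle. Short crisis stays that do not end HoT may fall inside the window.

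Readmissions are not ignored altogether. Their number and duration are a secondary outcome, and time to readmission is modelled, so readers will see a difference between arms even though it is not priced. Finally, the Dissemination section ties the hope for insurance cover to HoT being superior to TAU, without naming the cost result, so the cost result's role in reimbursement is partly an inference.

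What remains is that a comparison ending at an outcome-dependent date, with readmission unpriced, cannot support a general statement about cost.

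**Conclusion.** The point holds as a limit on interpretation, and the remedy is a cheap improvement. No cost after discharge is planned in either arm, and 28-35 of the 52 weeks to T5 carry no cost after regular HoT. The care left out is about 1.4-2.9 inpatient weeks per patient, against a HoT period of 12-16 weeks. That figure rests on the article's one-third yearly rate, even spread and assumed stays of 8-13 weeks; the lower rate in the article gives about 0.5-1.05. These are volumes per arm. The error in the cost difference depends on how far readmission differs between arms, which is not known in advance. The loss of ward costs after HoT discontinuation is conditional on what discharge means.

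**What to change.** Keep the randomization-to-discharge comparison, which answers the stated objective. Then:

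1. Add a comparison by randomized arm from randomization to T5: the HoT or TAU costs plus all psychiatric inpatient and day-patient days to T5, priced at daily rates.
2. State that inpatient care after HoT discontinuation counts in the HoT arm in both analyses, which also settles what discharge means for these patients in the costing.
3. Rest any general statement that HoT is less expensive on the T5 analysis, and word the discharge-limited result as cost during the differential treatment period.

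The cost is analysis-plan wording plus pricing of data already planned as the number and duration of rehospitalizations. It should be confirmed that day-patient readmissions are recorded there. There are two downsides. Costs come from the study centers, so stays at other hospitals need an assumed daily rate, with a range. Outpatient costs after discharge, which the protocol does not regulate and which may differ by arm, remain uncounted and should be stated as a limitation.
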